**RESEARCH PLAN**

We will perform the clinical studies at i) Alexishafen and Mugil Clinics, Madang Province, sites we have used for various studies since 2001 and which have proven recruitment potential and excellent facilities,CIA#31 and ii) Vunapope Hospital, East New Britain Province which also has a busy clinical load and laboratories which have been used by the PNG Institute of Medical Research (IMR) for malaria studies. Maprik in the East Sepik may be brought in as an additional site depending on recruitment. Laboratory studies (host/parasite genotyping, drug assays and/or biochemical testing) will be conducted at Vunapope; the IMR laboratories at Yagaum Hospital, Madang Province; the University of Western Australia (UWA) School of Medicine and Pharmacology and the Biochemistry Department at Fremantle Hospital; the Pharmacy School, Curtin University. Relevant techniques are well established in these institutions.

**Main Study: A trial of the tolerability, safety, efficacy and cost-effectiveness of AL, AP and AN in PNG children with uncomplicated falciparum or vivax malaria** *(Primary aim)*

*Background:* Since pyronaridine11-14 and naphthoquine16 are active against CQ-resistant falciparum malaria and have a t½*e* that is at least that of lumefantrine (4-6 days), AP and AN should have similar efficacy over 42 days of follow-up to AL in this situation. We postulated that the greater efficacy of DP vs AL against *P. vivax* reflects, in part, the longer piperaquine t½*e* (3-4 weeks), in which case the efficacy of AP and perhaps AN should equate with that of DP. However, the similar low efficacy of AL and CQ-SP in areas with known CQ-resistant *P. vivax* means that other factors may underlie the poor response to AL in our recent trial.8

*Operational principles:* We will conduct the study using standard operating procedures, under Good Clinical Practice guidelines, in accordance with the Helsinki Declaration, and with ethical approval from the PNG Ministry of Health Medical Research Advisory Committee and the UWA Human Research Ethics Committee. Although the trial is open-label, there will be an independent Data and Safety Monitoring Committee (DSMC) and external monitoring of sites.

*Endpoints:* The primary endpoint will be:

1. recrudescent *P. falciparum* within 42 days after correction for re-infections using PCR genotyping of polymorphic parasite loci19, 20 in children with falciparum malaria, or

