2. appearance of any *P. vivax* parasitaemia within 42 days after treatment for vivax malaria.

Secondary endpoints in falciparum malaria will be:

1. reappearance of PCR-uncorrected *P. falciparum* parasitemia,
2. appearance of any *P. vivax* parasitemia, and
3. appearance of *P. falciparum* gametocytes, all within 42 days.

Secondary endpoints in vivax malaria will be:

1. reappearance of any *P. vivax* parasitemia within 28 days, and
2. appearance of *P. vivax* gametocytes within 42 days.

Other secondary endpoints for each *Plasmodium* species will be initial fever and parasite clearance times (the times to the first of two consecutive assessments at which the child was afebrile and slide-negative, respectively), and drug safety including haemoglobin levels.

*Sample sizes:* Sample size calculations21 for the present trial are based on the assumptions that i) the *P. falciparum* Day 42 PCR-corrected ACPR for AL is 95.2%8 with a non-inferiority margin of 5% for AP and AN, ii) the *P. vivax* Day 42 uncorrected ACPR for AP and AN is at least double the 30.3% found previously for AL (as for DP in the original trial8), iii) there will be equal numbers in each treatment arm, and iv) there will be a 25% attrition rate:

| Study | Type | Total *n* | *n*/group with drop-outs | Power | Α |
| --- | --- | --- | --- | --- | --- |
| *P. falciparum* | Non-inferiority | 515 | 220 | >80% | 0.05 (one-tailed) |
| *P. vivax* | Superiority | 122 | 60 | >90% | 0.05 (two-tailed) |

*Subjects:* Children aged 0.5-5 years with an axillary temperature >37.5°C or fever during the previous 24 hours will be screened using on-site blood film microscopy. Those with either *P. falciparum* (>1000 asexual parasites/μL whole blood) or *P. vivax* (>250/μL) will be eligible if they have i) no features of severity,22 ii) not taken a study drug in the previous 28 days, iii) no clinical (including anthropometric) or laboratory evidence of another infection or co-morbidity including malnutrition. Informed consent will be obtained from parents/guardians.

*Clinical/laboratory procedures:* An initial (Day 0) history will be taken and physical examination performed. Blood will be taken for measurement of haemoglobin and glucose. Treatment allocation will be by computer-generated randomized design in blocks of 24 by site:

1. AL (Novartis Pharma, Basel, Switzerland) as artemether 1.7 mg/kg and lumefantrine 10 mg/kg twice-daily for three days,

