2. AP (Pyramax) as artesunate 3 mg/kg and pyronaridine tetraphosphate 9 mg/kg once-daily for three days, and
3. AN (Arco) as artemisinin 20 mg/kg and naphthoquine phosphate 8 mg/kg once-daily for three days (as justified above).

Combinations of full, half- or quarter-tablets will be swallowed whole or crushed lightly before administration. AL-treated subjects will be given tablets or suspension with milk; because there is no such recommendation for AP or AN, pharmacokinetic studies our group will perform during 2009 will determine whether these ACTs should also be given with milk. Only the evening AL doses will be unsupervised, being given at home by parents/guardians. Children vomiting within 30 minutes will be re-treated.

Standardized review including microscopy will be scheduled on Days 1, 2, 3, 7, 14, 28 and 42, with all data, including symptoms, unscheduled clinic visits and non-study treatment, entered on detailed case report forms. Children developing uncomplicated or severe malaria will be given DP at the clinic or intramuscular artemether at the local referral hospital, respectively as per the most recent PNG National Treatment Guidelines.23 All blood films will be re-examined by two skilled microscopists blinded to treatment. Slides discrepant for positivity/negativity, speciation or parasitaemia (>3x difference) will be adjudicated by a senior microscopist. The primary endpoints constitute ACPR under WHO-recommended assessment.24 Early treatment failure (ETF) will be taken as the development of severity or an inadequate parasitological response by Day 3. Any child developing parasitaemia between Days 4 and 42 will be considered late parasitological failure (LPF) or, if febrile, late clinical failure (LCF).

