Kaplan-Meier estimates will be computed for each endpoint by parasite species. Treatments will be compared by log-rank test. Safety and tolerability will be assessed from the incidence of symptoms/signs to Day 7 using Poisson regression (frequent events) or Fisher’s exact test (infrequent events). Blinded interim efficacy analyses and safety assessments will be performed under the auspices of the DSMC and the trial terminated prematurely if one treatment violates the non-inferiority margin or unexpected toxicity emerges. Comprehensive health care cost data will be collected for each patient from Day 0 to Day 42 as is being done currently for the previous trial,8 but indirect costs (e.g. reduced parental/guardian income due to the child’s illness) will also be ascertained in the present trial.

Cox regression using backward-stepwise modelling will be used to determine predictors of treatment failure among age, sex, measures of growth/nutrition, baseline haemoglobin, baseline parasitaemia, Day 7 partner drug concentrations and drug-specific IC50 values. We will utilise population pharmacokinetic modelling using NONMEM (Project Group, University of California San Francisco) and models of *P. falciparum* parasite development based on our animal studies to estimate MIC and derive secondary variables of clinical importance such as the time, in 48-hour parasite life-cycles, above MIC. We have performed host genotyping for red cell traits including thalassemia, South-east Asian ovalocytosis and Gerbich antigen blood group as predictors of response in previous studies and may, if other relevant pharmacogenetic data emerge, extend the proposed analyses to include other polymorphisms.

*Duration/feasibility:* The trial will run from June 2010 to June 2013. We recruited 742 eligible children at Alexishafen and Kunjingini in the East Sepik over 2.3 years in the initial trial,8 and foresee no difficulties in recruiting 870 children to the present study over 3 years. The longer time period for the new study allows for the effect of reduced local transmission when AL is introduced.

**Sub-study 1: Effect of treatment on gametocyte carriage during follow-up** *(Secondary Aim 3)*

*Hypotheses:* i) High field gradient magnetic fractionation (HFGMF) can be used to develop a simple but sensitive field test for gametocyte transmission; ii) AL, AP and AN have similar effects on gametocyte carriage for both *P. falciparum* and *P. vivax* infections.

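### One fixed, disclosed block size (24 by site) in an open-label trial lets a site tally reveal about 6% of assignments in advance: low severity, cheap to improve

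*Protocol*

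**What the plan says.** The allocation sentence is in the protocol's Research Plan, Main Study, under Clinical/laboratory procedures: "Treatment allocation will be by computer-generated randomized design in blocks of 24 by site". It gives one size and does not say that the size varies or is withheld from the sites. The number per arm within a block is not stated. It follows from the sample-size assumption that "there will be equal numbers in each treatment arm", so 24/3 = 8.

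Other parts of the Research Plan that bear on the point:

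- **Blinding and oversight** (Operational principles): "Although the trial is open-label, there will be an independent Data and Safety Monitoring Committee (DSMC) and external monitoring of sites".
- **Visibility of treatment** (Clinical/laboratory procedures): "Only the evening AL doses will be unsupervised, being given at home by parents/guardians". AL is given twice daily and AP and AN once daily, so the AL arm also differs in its visible schedule.
- **Judgement at enrolment** (Subjects): eligible children must have "no clinical (including anthropometric) or laboratory evidence of another infection or co-morbidity including malnutrition".
- **Outcome reading** (Clinical/laboratory procedures): "All blood films will be re-examined by two skilled microscopists blinded to treatment".
- **Size of the trial** (Duration/feasibility): the investigators "foresee no difficulties in recruiting 870 children to the present study over 3 years". The sample-size table gives 3 × 220 + 3 × 60 = 840, so both totals are used below.

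**The concern.** In a permuted block of known size, the end of the block is determined by what has gone before. Where treatment is visible, keeping a count is enough. Sealed envelopes or central allocation do not prevent this, because the information comes from past assignments and not from the list. The safeguards that the protocol names do not address it either: the monitoring committee and site monitoring do not stop anyone counting, and blinded re-reading of slides protects outcome assessment after enrolment.

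A person who expects a particular arm next could accept or defer a child with that arm in mind, for example through the clinical judgement in the eligibility criteria. Baseline parasitaemia is known from the screening film, and the protocol reports that it predicted outcome in DP-treated children in the previous trial. Selection of this kind happens before randomisation takes effect, and analysis cannot fully repair it. If higher-risk children were steered towards AL, the new combinations would look better on both the falciparum non-inferiority and the vivax superiority comparison. If they were steered the other way, the new combinations would look worse.

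**Working it through.** The block size is a design choice, so there is no plan figure to reproduce. The only check is that 24 divides evenly into three arms, which it does.

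**Inputs.** From the protocol: block size N = 24, arms k = 3, equal allocation (so m = 8 per arm), total 840 to 870. Assumed: the observer knows the size and sees every allocation on the list.

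**1. Assignments known with certainty.** These are the final run of a single treatment in each block.

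- Expected length = k·m/(N − m + 1) = 24/17 = 1.41 per block, and 1.41/24 = 5.9%.
- Chance that the run is at least 2: 3·8·7/(24·23) = 30.4%. At least 3: 3·8·7·6/(24·23·22) = 8.3%. At least 4: 2.0%. The last assignment of a complete block is always known.
- 840/24 = 35 blocks give 35 × 1.41 = 49 assignments. 870/24 = 36.25 blocks give 51. Incomplete last blocks are ignored.

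**2. Weaker foreknowledge.** Simulating 20,000 blocks of 8/8/8 gave 5.9% certain (agreeing with the formula), at least one arm excluded for 16.3% of assignments, and a best guess that is right 46.9% of the time, against 33.3% by chance.

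**3. Comparison with smaller fixed blocks.** The same formula gives 11.1% certain for blocks of 12 and 20% for blocks of 6. Twenty-four is already large for three arms.

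**4. What foreknowledge could do.** This is an illustration; every behavioural input is assumed. Staff act whenever the chance that the next child receives AL is 20% or less, or 50% or more, which occurs at about 27% of allocations. They then defer half of the children of the unwanted risk type.

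- Vivax: half the children are high-risk, with failure 90% against 40%. The false difference between AL and AP/AN is about 2.7 points. The planned difference is 2 × 30.3% − 30.3% = 30.3 points.
- Falciparum: a quarter are high-risk, with failure 9.6% against 3.2%. Overall failure is 0.25 × 9.6 + 0.75 × 3.2 = 4.8%, which matches the assumed 95.2% response. The false difference is about 0.3 points, against a margin of 5.

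**5. Randomly varying sizes.** Sizes are drawn from 15, 18, 21, 24, 27 and 30, and the guesser knows that set but not the order.

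| | Fixed 24 | Random 15–30, set known |
|---|---|---|
| Next arm certain | 5.9% | about 0.4% |
| At least one arm excluded | 16.3% | about 1.3% |
| Best guess correct | 47% | about 47% |
| Steering bias, vivax | 2.7 points | about 2.2 points |

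The remaining vivax bias is 2.2/2.7 = 81% of the original. It persists because the modelled steering responds to moderate odds, which random sizes hardly change, and not only to certainty. Other assumed sets also reduce certainty: 18/24/30 to about 1.1%, 12/18/24 to 1.7% and 6/9/12 to 2.3%. With 6/9/12, however, best-guess accuracy rises to about 53%, so small sizes are not an improvement on every measure.

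**The case against.** **The premises are partly assumed.** The protocol does not say who enrols, who holds the list or who gives the doses, nor that site staff know the block size. Alexishafen and Mugil are named together as the Madang location; if they share one list, neither clinic sees every allocation and the tally is harder there. This stands and limits the claim. The size is nevertheless printed in the study protocol without any statement that it is withheld.

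**The scope for selection is narrow.** Microscopy thresholds, severity and prior drug use are largely objective. The protocol reports that anthropometric features did not predict outcome before, and that baseline parasitaemia did so in DP-treated patients; DP is not an initial arm. Baseline factors are recorded, so gross steering would be partly visible. This also stands, and is a reason to rate the risk as modest.

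**The remedy removes little of the modelled bias.** This is correct when the set of sizes is known. It means that the sizes must be withheld as well as varied; it does not justify keeping one disclosed size.

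**Concealment steps belong in operating procedures.** Agreed. The absence of such steps is not part of this point, and they would not prevent counting in any case. The point rests on what the allocation sentence itself fixes and discloses.

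A reader might infer from the fixed block that the trial is likely to reach a false non-inferiority or false superiority result. The documents do not support that: the direction of any steering is unknown, the behaviour is hypothetical, and the illustrated bias is small beside the margin and the planned effect. Nor do they support stating as fact that the same staff screen, enrol and dose.

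**Conclusion.** The point holds as a low-severity design weakness with a cheap improvement. The predictability follows by arithmetic from the single size, equal arms and visible treatment. Whether anyone could use it depends on site staff knowing the size, seeing all allocations on their list and having a part in enrolment; these conditions are plausible but not documented. The bias figures rest entirely on assumed deliberate steering. Even so, they are unlikely by themselves to change either primary conclusion. Nothing in the protocol is contradictory or miscalculated here.

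**What to change.** Reword the allocation sentence to say that the computer-generated list uses randomly varying block sizes, in multiples of three, within each site. Remove the number 24 from the protocol, and record the sizes in a randomisation document that site staff do not hold. Both parts are needed: varying the sizes removes almost all certain foreknowledge, and withholding them deals with the guessing that variation alone leaves in place. Sizes around the present 24 (for example 15 to 30) serve better than small ones.

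The cost is one sentence and a regenerated list, with no extra children, staff or procedures. The one drawback is a slightly larger possible imbalance when a site stops in mid-block: at most 10 per arm with a largest block of 30 (30/3), rather than 8.

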At baseline and each subsequent visit, a finger-prick blood smear and filter paper blood spot will be taken, in addition to a 250 μL mixed capillary EDTA sample which will be centrifuged and the plasma separated. In addition, a 3-5 mL blood sample will be taken by venepuncture at baseline, day 7 and 28 for antimalarial drug assay. If a child presents with fever or has a positive blood film for malaria at other times, a single blood sample will also be taken – this will normally replace the day 28 sample if there is a re-infection/recrudescence which means the child has reached a pre-specified endpoint. The total volume of blood taken from any child will be <15 mL over 6 weeks. Although there is evidence that Day 7 plasma drug concentrations are independently associated with response for lumefantrine- and PQ-based ACT,25 there has been no study that has looked at pyronaridine or naphthoquine, or simultaneously incorporated other potentially important variables such as baseline *P. falciparum* parasitaemia in predictive models. Our finding that baseline parasitaemia predicted outcome in DP-treated patients8 should also be assessed simultaneously with other parasite- and drug-specific factors in a large patient sample and using other long-half life partner drugs. We did not identify anthropometric features that predicted outcome in our previous trial and postulate the same result with the newer regimens. Plasma drug concentrations at the time of treatment failure have been used qualitatively to identify resistant parasites, but no formal *in vivo* MIC estimate the has been derived.25

We have developed high performance liquid chromatography assays for lumefantrine, naphthoquine and pyronaridine,but now have access to liquid chromatography-mass spectrometry which allows greater assay sensitivity with a smaller sample volume and increased throughput. Day 7 and follow-up samples on the day of reappearance of parasitaemia will be taken from trial patients, centrifuged promptly, and separated plasma kept and transported frozen until assayed at Curtin University. Batches of each treatment will also be retained for assay of content. We have *in vitro* parasite culture facilities at Yagaum and these can be set up at Vunapope. We will utilise the *Plasmodium* lactate dehydrogenase colorimetric assay for drug sensitivity testing.

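### Allocation is blocked by site alone although each species is a separately sized comparison, and the stated log-rank test does not carry the site stratum: a minor weakness that is cheap to correct

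*Protocol*

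**What the plan says.** Allocation is fixed in the Protocol, RESEARCH PLAN, Main Study, under Clinical/laboratory procedures: "Treatment allocation will be by computer-generated randomized design in blocks of 24 by site". Species is not mentioned as a stratum. The sites are two clinics in Madang Province and one hospital in East New Britain, and "Maprik in the East Sepik may be brought in as an additional site depending on recruitment".

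Under Sample sizes, falciparum (non-inferiority, 220 per group with drop-outs) and vivax (superiority, 60 per group with drop-outs) have separate rows with their own power and alpha. Equal arms and 25% attrition are assumed for both. Under Subjects, eligibility rests on on-site blood film microscopy with a different density threshold for each species, so the species is known when a child is allocated.

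Under Data analysis: "Kaplan-Meier estimates will be computed for each endpoint by parasite species. Treatments will be compared by log-rank test". No stratification of that test is stated. The Cox model in the same section looks for "predictors of treatment failure among age, sex, measures of growth/nutrition, baseline haemoglobin, baseline parasitaemia, Day 7 partner drug concentrations and drug-specific IC50 values"; site is not in the list.

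**The concern.** Blocking within a site balances the arms over all children enrolled there, not within either species. Vivax children are about a fifth of the total, so they fall at scattered positions in the blocks, and much of the balance that blocking should give is lost in the smaller comparison. The sample-size assumption of equal arms is then met only on average.

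The second half concerns the test. The vivax primary endpoint is any vivax parasitaemia within 42 days, so a new infection counts as a failure and local transmission intensity enters the endpoint. Site is therefore plausibly prognostic, and it is already an allocation stratum. A log-rank test that leaves it out gives up some efficiency if sites differ.

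Efficiency matters because the vivax comparison has no power to spare, as the first step of the working shows.

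**Working it through.** **1. The plan's own vivax figure.** Inputs from Sample sizes: AL response 30.3%, comparator at least double (60.6%), two-sided alpha 0.05, 60 per group, 25% attrition. Evaluable per arm: 60 × 0.75 = 45. Two-proportion power is Φ[(d − 1.96·SE0)/SE1], with SE0 pooled and SE1 unpooled.
- d = 0.606 − 0.303 = 0.303; pooled proportion 0.4545.
- SE0 = √(0.4545 × 0.5455 × 2/45) = 0.1050.
- SE1 = √[(0.303 × 0.697 + 0.606 × 0.394)/45] = 0.1000.
- Φ(0.973) = 83.5%.

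The stated power above 90% is reached only if all 60 are evaluable (92.5%). That is a separate point; here it sets the baseline.

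**2. Vivax arm sizes under site-only blocks.** Planned total: 3 × 220 + 3 × 60 = 840, of which 180 are vivax. Assume three equal sites of 280. If the 180 vivax children fall at random over 840 allocations balanced across arms, the difference between two arms has variance 2 × 60 × (660/839) = 94.4. This matches three independent arms with SD √(94.4/2) = 6.87. The range of three normal values has median 1.59 SD and 95th percentile 3.31 SD:
- median gap 1.59 × 6.87 = 10.9;
- 95th percentile 3.31 × 6.87 = 22.7.

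Simulation of actual 24-child blocks gives the following:

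| Blocks | Gap, median | Gap, 95th percentile |
| --- | --- | --- |
| By site | 11 | 23 |
| By site and species | 3 | 7 |

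With site-only blocks and the vivax total held at 180, the smallest arm has median 55 and 5th percentile 48, and is 50 or fewer in 13% of trials. If the vivax total also varies by chance, the 5th percentile is about 46.

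**3. What the imbalance costs.** The same formula with unequal evaluable arms (AL first):
- 45 and 45: 83.5%
- 40 and 50: 82.9%
- 35 and 55: 81.5%

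Over simulated trials (870 children, about 62 vivax per arm), the loss from unequal arms alone averages 0.2 points, with 95th percentile 0.9 and 99th percentile 1.5. Allocation stays random, so there is no bias.

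**4. Site-stratified against unstratified test, vivax.** The protocol gives no site rates, so all of these are assumed. Setting: three equal sites, site-only blocks, about 45 evaluable per arm, Day 42 response as a binary stand-in for the log-rank test, Mantel-Haenszel against unadjusted, 6,000 runs per row.

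| AL response by site (assumed) | Unstratified | Stratified | Difference |
| --- | --- | --- | --- |
| equal, 30.3% | 83.7% | 82.8% | −0.9 |
| 20 / 30 / 41% | 83.0% | 83.7% | +0.7 |
| 12 / 28 / 51% | 83.5% | 87.5% | +4.0 |
| 7 / 25 / 59% | 83.6% | 91.0% | +7.4 |

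Type I error of the unstratified test was 4.3% to 5.1%. A time-to-event simulation read at Days 7, 14, 28 and 42 (1,500 runs) agrees in direction: 86% unstratified against 84% stratified with equal sites, and 86% against 90% with AL failure of 50/70/89%.

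If the two Madang clinics are alike and only the provinces differ, a gap of 14 to 16 points costs the unstratified test under 1 point of power, and a 30-point gap about 3 to 4.

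**5. Falciparum.** With mean failure 4.8% and assumed site rates of 2/4.8/7.6%, the between-site variance is (0.028² + 0 + 0.028²)/3 = 0.00052. Total variance is 0.048 × 0.952 = 0.0457. The ratio is about 1%, so stratification changes little here.

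**The case against.** The strongest reply is that both halves rest partly on silence. The protocol does not say that one list serves both species, and it tabulates them as separate studies. Whether a log-rank test is stratified is ordinary content for a statistical analysis plan; the protocol refers to an a priori plan that is not shown. This stands for the test: a stratified version may already be planned. It carries less weight for allocation. The strata belong in the protocol, site is the only one named, and no analysis plan can restore species balance after enrolment.

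The second reply is that the harm is small or hypothetical. That also stands. Unequal arms cost almost nothing, and a material gain from stratifying needs response to differ by roughly 40 to 50 points over three sites, or about 30 between the provinces.

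A reader might infer more than the documents support:
- *That the scheme itself unbalances the vivax arms or biases the comparison.* It leaves balance to chance, without bias.
- *That ignoring site invalidates the test, mis-states precision or distorts the effect.* The test holds its level. A marginal hazard ratio lies closer to the null than a site-specific one, but it is a different estimand; the risk difference has no such attenuation.
- *That a large loss of power is established.* Assumed failure of 35/75/95% by site gives 84% against 95%, but nothing in the protocol supports a 60-point spread.
- *That the stepwise Cox search is the only covariate model.* The two sub-studies describe others, and the search is for predictors of failure, not the treatment comparison.
- *That adjustment for baseline parasitaemia is required.* The remark "Our finding that baseline parasitaemia predicted outcome in DP-treated patients" concerns a drug that is not an initial arm, and parasitaemia is already a Cox candidate.

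**Conclusion.** The point holds as a minor design weakness. Site is the only stated blocking factor, although the vivax comparison is sized separately, assumes equal arms, and concerns children whose species is known before allocation. The arm-size results assume three equal sites and 180 vivax children among 840, or the same mix among 870. The consequence is untidy arm sizes, not bias or a material loss of power.

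For the test, the case is one of low cost against possible gain: about 0 to 2 points of vivax power lost if sites are alike, roughly 3 to 7 gained if they differ widely. The gain depends wholly on assumed site rates, and with modest differences it is close to zero. For falciparum the change is mainly one of consistency with the allocation.

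**What to change.** - **Clinical/laboratory procedures:** state that separate blocked lists are kept for each site and species. With three sites this means six lists instead of three, with a few more incomplete blocks. For example, 60 vivax children at a site fill two and a half blocks of 24.
- **Data analysis:** state that the log-rank test, or a Cox model used for the treatment comparison, is stratified by site, and that falciparum non-inferiority is assessed on a site-stratified risk difference (Mantel-Haenszel or inverse-variance weights). If the unseen analysis plan already says this, a cross-reference is enough. The cost is one line of code and at most 1 to 2 points of vivax power if sites do not differ.

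If enrolment has already run on site-only lists, the allocation cannot be changed in retrospect, but the stratified analysis can still be specified before the data are examined by arm.
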